## Methods/design

### Preregistrations and current protocol

The study was preregistered on May 25th, 2021, prior to the inclusion of the first patient (ClinicalTrials.gov: NCT04900064). Before this, the study was outlined in an ethical review application to the Swedish Ethical Review Board (2020–04198) on October 12th, 2020. This is the first version of the study protocol (1.0), developed toward the conclusion of the data collection phase. It was submitted for publication on March 18th, 2025, prior to the inclusion of the final participant, and will shortly thereafter, without any changes, be made publicly available as a preprint in an open-access repository. The protocol serves to provide detailed specifications on the study methods and analyses before analyses start. It has been developed in accordance with the SPIRIT guidelines [28].

While this protocol, the preregistration and the ethical review application largely align, some differences exist. Due to challenges in performing the coding practice for which patients in the core PCBH arm would be suitable for structured interventions, identified in a pilot study to this trial, the comparison based on that coding is now classified as secondary instead of primary. Additionally, some implementation outcomes outlined in the preregistration – such as whether the implementation of GSH increases waiting times – will be excluded due to inherent limitations of the study design, where the presence of two parallel care models within the same center renders any results from these outcomes non-informative. Research questions regarding variations in what proportion of patients are assessed as suitable for GSH, adherence to GSH principles, between-center variation and therapist effects (questions 5–9 above) have been added, following observations during clinical supervision throughout the trial. Trial reports will include a dedicated section for reporting deviations.

### Design and overall procedure

The proposed study is a single-blind, multicenter, randomized clinical trial with a 1:1 allocation ratio at the individual level. It will feature two study arms and four measurement points. Potential participants will be identified prior to their first visit. For those who provide written consent, the pre-treatment assessment will be conducted either shortly before or within seven days of their initial visit. This flexibility is necessary to accommodate the typically very brief waiting period between patients’ self-referrals and their first visit. Follow-up assessments will be conducted at 4, 8, and 12 weeks, with the 12-week point serving as the primary endpoint. Standard Operating Procedures (SOPs) will be implemented to ensure consistency in key procedures, and digital Client Report Files (CRFs) will be maintained on the study’s technical platform. Participants will be randomly assigned to one of two study arms:

Core PCBH model (PCBH): All patients undergo a contextually based interview (described below) to assess their concerns, symptoms, context and values, and are then offered BI. Retrospectively, patients are assessed to determine whether they would have been indicated for a structured, protocol-based treatment. However, this does not affect which intervention they receive, as all patients are given BI.Extended PCBH model (PCBH + GSH): PCBH practices are complemented with an extended assessment, including a brief, standardized diagnostic procedure to determine if GSH is a suitable treatment option for the patient. Patients that are deemed suitable for and accept GSH as an intervention receive a condition-specific self-help manual along with clinician guidance; those not suitable receive BI.

This means that patients are not randomized between treatments, but between models of care (PCBH vs. PCBH + GSH). In the extended arm (PCBH + GSH), patients will receive either GSH or BI based on their assessed suitability for GSH treatment. Suitability in this context means that the patient is both interested in and capable of engaging in a self-help treatment and has a primary problem related to mood, anxiety, stress-related conditions, or insomnia. In contrast, the core PCBH arm will include only patients who have received BI. However, within this group, there will be patients would have been suitable for GSH if it was available to them. After data collection is complete, these patients will be retrospectively identified using a standardized procedure that as closely as possible mirrors the extended assessment in the PCBH + GSH model. This approach will allow us to address the secondary research question [2] regarding the subgroup of patients suitable for GSH. The retrospective assessment can determine whether the patient’s primary problem falls within the specified categories and identify any clear indications that they would not be capable of engaging in treatment. However, patient preferences remain unknown, as they were never offered the option. Refer to Table 1 for an overview of the patient groups, along with the codes used to identify them.

**Table 1 Tab1:** Patient groups by randomization, indication for structured interventions, and treatment given

Model of care	Indicated for a structured intervention	Treatment received	Code
**Core PCBH**	Indicated	BI	CORE-I-BI^1^
	Not indicated	BI	CORE-N-BI^2^
**Extended PCBH**	Indicated	GSH	EXT-I-GSH^3^
	Not indicated	BI	EXT–N-BI^4^

^1^Retrospectively indicated for a structured intervention for mood, anxiety, stress-related conditions, or insomnia but received brief interventions (BI)

^2^Retrospectively not indicated for a structured intervention and received brief interventions (BI)

^3^ Assessed by the clinician as indicated for a structured intervention and received guided self-help (GSH)

^4^ Assessed by the clinician as not indicated for a structured intervention and received brief interventions (BI)

Note: In the Core PCBH arm, indication for a structured intervention is assessed retrospectively by an expert rater. In the Extended PCBH arm, indication is assessed in real-time by the regular care clinician

### Enrollment of PCBH PCCs

PCCs that have already implemented and consistently adhere to the PCBH model are eligible for inclusion in the trial. The PCCs in this study adhere to a PCBH model adapted to the Swedish healthcare system [29]. To ensure adherence, a qualitative evaluation of PCBH fidelity will be conducted at each participating PCC by one of the authors ([name]) prior to trial inclusion. This evaluation will involve assessing key aspects of PCBH implementation, including the integration of at least one BHC who is skilled in delivering BI. A list of study sites is available at the Clinical Trials preregistration.

### Participant recruitment

Trained research assistants will gain access to the PCC’s booking systems and will twice a day scan the schedules of BHCs to identify, contact and randomize potential participants. All patients aged 18 and older who are deemed suitable for mental or behavioral health interventions – as assessed by nurses or other PCC staff as part of standard routines – will be provided with information about the study. This applies regardless of their stated reasons for seeking healthcare, potential diagnoses, or concurrent medical treatments. The inclusive eligibility criteria align with the naturalistic setting and aim of the PCBH model. However, patients who are already undergoing psychotherapeutic treatment or have visited BHCs at the PCC for the same reason within the past three months will not be eligible for participation. Patients will primarily be contacted by phone, with text messages used as an alternative if they are difficult to reach. Contact attempts will begin as soon as patients are identified and will continue until their first visit has passed. All identified patients will receive digital access to written information about the study, consent forms, and pre-measure screening tools via the phone call or text message.

### Randomization and blinding

The independent Karolinska Trial Alliance (KTA) has set up a randomization system on the website randomize.net, based on list randomization with even blocks of random sizes determined by KTA and not shared with the researchers. Research assistants, who are not involved in other aspects of the trial and have limited knowledge of the differences between the study arms, will conduct each individual randomization using this website. The platform ensures concealment and integrity by performing real-time allocation, revealing the treatment assignment only after participant enrollment, and maintaining a comprehensive audit trail with timestamps and user activity logs. To minimize placebo and nocebo effects, participants will remain blind to the availability of different treatment options in the study arms. They will be briefly informed that the PCC is evaluating two types of assessments, both more comprehensive than standard routine. As the PCBH arm also includes extensive pre-treatment questionnaires, which are not part of standard PCBH procedures at the PCCs, this design ensures that both study arms are perceived by participants as offering a more thorough assessment. However, participants will not be told which assessment they were allocated to, ensuring blinding to both the type of assessment and treatment options.

Given the prompt availability of PCBH PCCs, often providing same-day appointments, it is worth noting that participants in this study are randomized immediately upon identification, even before completing the pre-measure. The randomization result is noted in the clinician’s schedule, allowing them to conduct assessments in accordance with the randomization during the initial visit. However, only patients who consent to the study and fill in the pre-measure will be included in analyses.

### Models of clinical assessment

#### Contextual assessment (Core PCBH arm)

Clinicians in PCBH place a significant importance on understanding the patient’s current context and their strategies for managing stressors and unwanted experiences. The therapist explores the patient’s life context using a semi-structured interview called the Contextual Interview (CI), focusing on finding what triggers the unwanted experiences, when and how often they occur, and the trajectory of the problem. The goal is to promote a person-centered, whole-person perspective, while collecting clinically relevant information (such as avoidance behaviors, life skill deficits and dysfunctional coping strategies) to facilitate individually tailored interventions. In this model, the CI is regarded as a therapeutic intervention in its own right as opposed to a way of merely collecting information, as it broadens the patient’s perspective, helping them see their symptoms and problems within a wider context [29]. This shift in perspective is thought to foster insights that may inspire new ideas or behaviors. As such, a collaborative effort to identify and introduce an intervention is made during the first visit, directly after the CI. While the initial assessment and first intervention are typically completed within a single half-hour visit, both the assessment process and intervention strategies can be further refined during subsequent patient visits if needed. In contrast to the diagnostic assessment described below, the clinician pays little attention to whether the patient fulfils the criteria for a psychiatric diagnosis. In this study, clinicians do however have access the answers of the pre-treatment questionnaires, including the result of the automated diagnostic screening algorithm, and choose freely if they use them. As the study is integrated into routine healthcare, patients requiring more specialized care will be referred to an appropriate level of care irrespective of their randomization assignment.

#### Extended diagnostic assessment (Extended PCBH arm)

Manualized CBT operates within the medical model of psychiatry, which means that the aim of treatment is to achieve remission of an identified disorder or condition [1]. It is therefore seen as pertinent to assess which diagnosis a patient suffers from, so that the correct protocol can be chosen. The demands for a structured assessment are even greater in GSH, as the standardized self-help material limits the possibility for re-assessment, adaptions and individualization of content during treatment.

In this study, the diagnostic assessment consists of three parts: an automated algorithm described below (see Measures), based on patients’ pre-treatment self-ratings to screen for diagnoses and overall suitability for GSH, an interview focused on the patient’s medical history, symptoms and life context, and the use of selected parts of Mini-International Neuropsychiatric Interview (M.I.N.I.) [30] based on which problem areas the algorithm identified as relevant. The assessment takes place over two 30-minute visits. A key difference between the two types of assessment is that, in the diagnostic assessment, there is a clear distinction between assessment and intervention. The assessment is completed first, and only after that is a decision made about which interventions to proceed with at a subsequent visit. While some questions may naturally overlap (such as those regarding the life context), in this form of assessment, they are primarily seen as a means of gathering information rather than initiating an intervention.

The clinician is instructed to always use the results of the automated algorithm to inform the focus of the M.I.N.I. interview. As the GSH treatments in this study are possible to use with subclinical problems, the goal of the assessment is not necessarily for the patient to meet a specific diagnosis but rather to pinpoint the problem area most relevant to the patient’s concerns. The diagnostic evaluation concludes with the clinician providing feedback to the patient regarding the assessment results and, when appropriate, offering GSH for the identified condition. If GSH is not a good fit or the patient declines the treatment, they are offered BI. In such cases, BI may be initiated during the first visit if time permits or is otherwise scheduled for a follow-up appointment. Clinicians may also bypass the diagnostic assessment and proceed directly with BI if it is clear from the outset that the patient is unsuitable for GSH. Examples of this are if the patient’s primary concern clearly falls outside the issues addressed by the GSH materials used in this study (for example substance abuse). As in the contextual assessment, patients requiring specialized care will be referred accordingly.

### Interventions

#### Brief interventions (BI)

Typically spanning from a single to a few sessions, BI are customized to meet the immediate needs and objectives of the patient. Based in the contextual assessment, clinicians collaborate with patients to conceptualize the problem as well as establish a plan with achievable goals. Psychoeducation, reframing, normalization, and validation often play important roles in these interventions, providing patients with an understanding of how their problems interact with their inner and outer context. Additionally, BI often incorporate skill-building techniques. Common clinical practice include using chosen parts of ESTs (for example, working with behavioral activation or exposure principles, but not following the recommended session length or amount), or using treatment options designed to be brief, such as Focused Acceptance and Commitment Therapy (FACT), which emphasizes mindfulness, acceptance, and value-based action to help individuals develop psychological flexibility [31]. Following the initial intervention, clinicians may schedule follow-up appointments or check-ins to evaluate progress, reinforce learning, and make any necessary adjustments to the treatment plan.

#### Guided self-help (GSH)

In this study, GSH is administered through self-help books tailored to specific disorders and supplemented with both individual 30-minute guiding sessions (conducted in-person or via video) and shorter 15-minute follow-ups (conducted over the phone or through brief video calls). Each GSH treatment contains between 3 and 6 contacts, of which a minimum of 1 and a maximum of 3 are longer guidance sessions. In contrast to BI practices, all guiding sessions are pre-planned at the outset of treatment. These are scheduled at key points in treatment, such as when the patient is starting exposure exercises in GSH targeting anxiety. The brief check-ins do not have to be pre-planned but can be incorporated as needed throughout the treatment, allowing for increased frequency for patients who require additional support. The role of the therapist is to motivate the patient to follow the program, especially during more demanding parts of the treatment, and to actively engage in practicing challenging exercises together with the patient. Each chapter of the books corresponds to the content of one session of face-to-face CBT, featuring psychoeducation, and practical exercises for documenting and challenging thoughts, emotions, and behavioral patterns contributing to the disorder. Typically, patients progress at a pace of one chapter per week, though this tempo can be adjusted based on individual needs.

GSH is offered using CBT self-help books for depression [32], generalized anxiety and worry [33, 34], illness anxiety disorder [35], social phobia [36], panic disorder [37], OCD [38], stress, adjustment disorder and exhaustion disorder [39], and insomnia [40]. All used books have been previously evaluated in research to ensure their efficacy and suitability, either in book format or text-based internet treatments [24, 32, 34, 41–46]. For depression and worry, the project has self-printed books based on internet treatments. For the depression book, some modifications were made to the original text, incorporating a stronger values-based component in behavioral activation, rather than focusing solely on increasing positive reinforcement [47]. The generalized anxiety and worry book underwent only minor changes to improve its appearance in print, with the content largely unchanged [34].

#### Training and supervision

As noted above, only PCCs with high fidelity to the PCBH model are selected for the study, aiming to ensure that clinicians are proficient in delivering BI. Recently hired clinicians with limited experience in PCBH or BI are provided with six half-day training sessions. Additionally, all participating clinicians receive at least monthly supervision in BI as part of their routine practice. However, diagnostic assessments and GSH are expected be new to the clinicians in PCCs operating under the PCBH model. As such, all clinicians undergo a 4-hour online training covering diagnostic assessment and general principles for GSH. They receive copies of all books used within the GSH treatment with reading instructions, as well as recorded lectures on the books and underlying evidence. Additionally, every book comes with a brief clinician’s guide, delineating important treatment components and when guidance sessions should be booked. Throughout the study duration, clinicians administering GSH to patients receive 45-minute clinical supervision sessions every two weeks in addition to any supervision they have in their clinic.

### Measures

#### Sociodemographic and clinical data at baseline

Self-reports will be used to gather information on relationship status, education, occupation, financial stability, emotional and practical support, and living arrangements. Additionally, self-reports and medical records will be utilized to document the main reason for the visit, problem duration, other health concerns, concurrent care, ICD-10 diagnoses, and medications. These forms are available in the Supplementary materials A.

#### Patient outcomes

Patient outcomes will be primarily assessed through self-report forms, complemented by a semi-structured interview to gather more detailed information about the patient experience. Self-report measures are completed at the pre-measure timepoint – prior to or shortly after the initial visit at the PCC – with follow-ups at 4 weeks (FU4), 8 weeks (FU8), and 12 weeks (FU12), with FU12 serving as the primary endpoint. A long-term follow-up is conducted one year later (FU52). The number of visits and contacts during this period is variable in both BI and GSH treatments. All timepoints are relative to the completion of the pre-measure. The interview, available in the Supplementary materials B, is conducted at the FU12 timepoint and allows patients to provide detailed feedback on their satisfaction, adverse events, treatment content, goals, and perceived changes in symptoms and quality of life.

##### Everyday functioning – Primary outcome

The primary patient outcome is everyday functioning, assessed through 8 out of 12 items covering four domains of the WHO Disability Assessment Schedule 2.0 (WHODAS-12) [48]: Life activities, Cognition, Getting along, and Participation, together reflecting psychosocial functioning. The Mobility and Self-care domains, more representative of physical functioning, have been found to constitute independent factors in mental health patients [49] and are expected to remain relatively stable throughout treatment. Hence, they will be excluded in primary analyses, but will be included in secondary analyses for better comparability with other trials.

##### Symptoms

Abbreviated versions of established patient-rated questionnaires for prevalent mental health disorders will be used to measure symptoms. See Table 2 for an overview, including timepoints and cut-off scores. Each scale score will be normalized to a range of 0 to 1 by dividing it by the scale’s maximum value. This normalized value will be used in two ways:

Primary symptom: Patients indicated as suitable for structured treatments (the CORE-I-BI and EXT-I-GSH groups) will have their primary symptom measure determined based on which GSH intervention is deemed most suitable for them. The stress and exhaustion areas, which are closely related and treated using the same GSH protocol, are assessed using two separate scales. The primary symptom measure is the averaged value of both scales, though they will also be analyzed separately. Patients indicated for BI (the CORE-N-BI and EXT-N-BI groups) will not have a value for this measure.General symptom index: A composite measure will be calculated by averaging the normalized scores across all symptom scales at each measurement point. To prevent the similar scales of stress and exhaustion from disproportionately influencing the overall measure, their average will be used as a single combined score in the general symptom index. AUDIT-C and the pain scale will be excluded, as substance use and pain are not targeted by the interventions.

**Table 2 Tab2:** Overview of patient questionnaires including scale origin, algorithm cut-offs, and administration timepoints

Self-report questionnaires	Origin	Algorithm cut-off	PRE	FU4	FU8	FU12	FU52
*Functioning*,* quality of life and health behaviors*							
Brunnsviken Brief Quality of Life Scale 12-items (BBQ)	PUB		X			X	X
DAily Routines for Well-being INventory 13-items (DARWIN)	CON		X			X	X
Outcome Rating Scale 4-items (ORS)	PUB		X	X	X	X	X
World Health Organization Disability Assessment Schedule 2.0 12-items (WHODAS 2.0)	PUB		X			X	X
**(Primary Outcome) World Health Organization Disability Assessment Schedule 2.0 8-items (WHODAS 2.0)**	**PUB**		**X**	**X**	**X**	**X**	**X**
*Symptoms*							
Alcohol Use Disorders Identification Test-Concise (AUDIT-C-3)	PUB	3–4^1^	X	X	X	X	X
Generalized Anxiety Disorder 2-item (GAD-2)	PUB		X	X	X	X	X
Generalized Anxiety Disorder 7-item (GAD-7)	PUB	9	X			X	X
Insomnia Severity Index 2-item (ISI-2)	PUB	4	X	X	X	X	X
Karolinska Exhaustion Disorder Scale 3-item (KEDS-3)	CON	11^2^	X	X	X	X	X
Obsessive Compulsive Disorder 3-item (OCD-3)	CON	3	X	X	X	X	X
Pain (One-item rating from 0 to 10)	CON		X	X	X	X	X
Panic Disorder Severity Scale 2-item (PDSS-SR-2)	EMP	2	X	X	X	X	X
Patient Health Questionnaire 2-item (PHQ-2)	PUB		X	X	X	X	X
Patient Health Questionnaire 9-item (PHQ-9)	PUB	8	X			X	X
Perceived Stress Scale 3-item (PSS-3)	CON	8	X	X	X	X	X
Short Health Anxiety Inventory 3-item (SHAI-3)	EMP	3	X	X	X	X	X
Social Phobia Inventory – Abbreviated Version (Mini-SPIN-3)	PUB	5	X	X	X	X	X
*Questionnaires used for health economic analyses*							
EuroQol-5 Dimensions (Eq. 5D)	PUB		X			X	X
Trimbos/iMTA questionnaire for Costs associated with Psychiatric illness (TiC-P)	PUB		X			X	X
Question about sick leave 1-item				X	X		
*Treatment credibility*,* satisfaction and adverse events*							
Adverse events 3-item	CON			X	X		
Adverse events 9-item	CON					X	
Assessment of goal achievement (Evaluation of change) 2-items	CON					X	
Assessment of your mental health care at the PCC 9-items	CON					X	
Client Satisfaction Questionnaire (CSQ) 4-items	CON					X	
Patient Global Impression Improvement 1-item (PGI-I)	PUB			X	X	X	X
Session Rating Scale 5-items (SRS)	PUB			X	X	X	
Treatment Credibility Scale 5-items	PUB		X				
*Sociodemographic and clinical data*							
Background questions 10-items			X				
Questions about care outside the study 4-items						X	
Questions about health issues and care 6-items			X				

^1^ The cut-off is set to 4 for men and 3 for women as well as patients with other gender identities

^2^ To reach the cut-off, it is also required that the patient attributes their symptoms to long-term stress

Note: The origin of the measure is defined as follows: PUB (published and empirically tested); EMP (created empirically through factor analytic item-reduction and sensitivity-to-change analyses on large datasets from previous trials conducted by the research group, not yet published); CON (created through consensus by the researchers or an expert group, not yet published or empirically tested)

The symptom scales are also used by the automated algorithm to help identify patients’ main areas of concern. If a patient scores above the cut-off specified in Table 2, points will be added to an overall score reflecting the relevance of the problem area for the patient. This process is further detailed below. The cut-offs, set by the research group, are not intended to indicate likely diagnoses but to highlight problem areas that may be significant for the patient. When available, established cut-offs have been used –however, these have been adjusted for the purpose of this study when necessary, for example to achieve a better balance between the problem areas. In cases where no established cut-offs exist, the research group has reached a consensus to define appropriate thresholds. This tailored approach enhances the algorithm’s ability to identify clinically meaningful issues while minimizing false positives for common experiences. The symptom scales, their cutoffs and their use in the algorithm were tested in a pilot study (manuscript in preparation). However, three scales measuring symptoms of stress, exhaustion disorder and OCD were adjusted or replaced based on clinical observations during the pilot study. The modifications aimed to enhance clinical relevance and ensure that the scales more accurately capture the core symptoms of each condition.

The PHQ-9 is a self-report tool used to assess the severity of depression symptoms over the past two weeks [50]. It consists of nine questions covering common symptoms of depression, such as low mood, loss of interest or pleasure, and changes in appetite or sleep patterns. The GAD-7 is a questionnaire designed to measure the severity of generalized anxiety disorder symptoms [51]. It comprises seven items assessing symptoms such as nervousness, worrying, and restlessness over the past two weeks. PHQ-2 and GAD-2 are concise versions incorporating two items from each of these scales, assessing depression and anxiety symptoms [52, 53], together forming the PHQ-4 scale [54]. The PDSS-SR-2 is a two-item scale used to assess the severity of panic disorder symptoms, measuring the frequency and severity of panic attacks over the past week [55]. Mini-SPIN is a 3-item questionnaire used to assess symptoms of generalized social anxiety disorder, evaluating fear, avoidance, and physiological symptoms related to social situations [56]. ISI-2 is a shortened version of the Insomnia Severity Index used to assess the severity of insomnia symptoms [57]. It consists of two items evaluating the severity of difficulty falling and staying asleep. AUDIT-C is a brief screening tool used to assess alcohol consumption patterns and identify individuals at risk for alcohol-related problems [58]. It consists of three questions assessing alcohol consumption, frequency of binge drinking, and alcohol-related problems. Bodily pain was measured with a 10-point Likert scale, where 0 indicates no pain over the past two weeks and 10 represents the worst pain imaginable during the same period.

For illness anxiety disorder, stress, exhaustion disorder, OCD and pain, there is a lack of validated ultra-brief scales. In these cases, scales have been developed through one of three approaches: (1) factor analytic item-reduction and sensitivity-to-change analyses on large datasets from unpublished studies conducted by the research group (2), expert consensus to select items from longer validated scales, or (3) expert consensus to create entirely new brief scales. The SHAI-3 contains 3 items [5, 7, 10] from the SHAI-14 [59], measuring symptoms of illness anxiety disorder, selected through factor analysis. To measure stress and exhaustion, three items [3, 8, 9] were selected from the Perceived Stress Scale-14 [60] and three [1, 4, 5] from the 9-item KEDS [61], which assesses symptoms of exhaustion disorder, forming the PSS-3 and KEDS-3 instruments, respectively. These items were selected by the research group in collaboration with a leading expert in Swedish stress research to capture the patient’s intuitive experience of stress, while minimizing overlap with closely related disorders. A brief measure used to assess symptoms of obsessive-compulsive disorder was developed together with a leading Swedish OCD researcher. The measure consists of a description of obsessive thoughts and compulsions with examples of common themes and behaviors, asking if the patient has had any obsessive thoughts or compulsive behaviors and if so, how uncomfortable or difficult the experience has been. The OCD scale is available in Supplementary materials C.

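### As worded, the general symptom index counts depression and worry twice at PRE, FU12 and FU52 but once at FU4 and FU8, so its composition changes over time

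*Protocol article*

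**What the plan says.** The section on symptoms (Protocol article, Measures, Patient outcomes) puts every scale on a common footing: "Each scale score will be normalized to a range of 0 to 1 by dividing it by" its maximum. Each scale therefore enters an average with equal weight, whatever its number of items.

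The index is then defined: "A composite measure will be calculated by averaging the normalized scores across all symptom scales at each measurement point". Two qualifications follow:

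- Overlap: "To prevent the similar scales of stress and exhaustion from disproportionately influencing the overall measure, their average will be used as a single combined score".
- Exclusions: "AUDIT-C and the pain scale will be excluded, as substance use and pain are not targeted by the interventions".

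Table 2 has separate rows for PHQ-2, PHQ-9, GAD-2 and GAD-7 in its symptom block. PHQ-2 and GAD-2 are marked at PRE, FU4, FU8, FU12 and FU52. PHQ-9 and GAD-7 are marked at PRE, FU12 and FU52 only. The text confirms that the forms are nested: "PHQ-2 and GAD-2 are concise versions incorporating two items from each of these scales".

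Nothing in the article says which version of PHQ or GAD enters the index. For WHODAS, where a short and a long version also coexist, the section on everyday functioning does say which version serves the primary and which the secondary analyses.

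**The concern.** A composite followed over time should be the same quantity at each visit. Under the stated rule it is not, because two components drop out at FU4 and FU8 and return at FU12. Part of any movement in the index between PRE and FU4, or between FU8 and FU12, would then come from the formula and not from the patients.

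The rule also gives depression and worry two votes each at PRE, FU12 and FU52, with two items of each long form entering twice. The plan merges stress and exhaustion because two similar scales would otherwise weigh too much. That reason applies with more force to pairs of scales that share items, yet no such step is taken for them.

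At stake are the description of symptom course within each arm and the meaning of the index at FU12.

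**Working it through.** **Inputs.** The index rule, the exclusions and the stress/exhaustion merge come from the section on symptoms. The schedule comes from Table 2. The plan states no figure for the index, so there is none to reproduce.

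**Step 1: count the components.** Drop AUDIT-C and pain, and merge PSS-3 with KEDS-3.

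| Component | PRE, FU12, FU52 | FU4, FU8 |
|---|---|---|
| PHQ-2 | yes | yes |
| PHQ-9 | yes | no |
| GAD-2 | yes | yes |
| GAD-7 | yes | no |
| ISI-2 | yes | yes |
| Mean of PSS-3 and KEDS-3 | yes | yes |
| OCD-3 | yes | yes |
| PDSS-SR-2 | yes | yes |
| SHAI-3 | yes | yes |
| Mini-SPIN | yes | yes |
| **Total** | **10** | **8** |

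**Step 2: derive the weights.**

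- Depression: 2/10 = 20% against 1/8 = 12.5%. Worry has the same weights.
- Depression plus worry: 4/10 = 40% against 2/8 = 25%.
- Each other domain: 1/10 = 10% against 1/8 = 12.5%.

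**Step 3: shift for a patient with no change.** Let *a* be the mean normalised depression/worry score and *b* the mean of the other six components. Assume that short and long forms have the same normalised mean.

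- PRE index = 0.40*a* + 0.60*b*
- FU4 index = 0.25*a* + 0.75*b*
- FU4 minus PRE = -0.15 × (*a* - *b*)

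The documents give no means, so the values below are assumptions that show the range.

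| *a* | *b* | PRE | FU4 | Shift |
|---|---|---|---|---|
| 0.60 | 0.20 | 0.360 | 0.300 | -0.060 |
| 0.60 | 0.30 | 0.420 | 0.375 | -0.045 |
| 0.50 | 0.25 | 0.350 | 0.3125 | -0.0375 |
| 0.50 | 0.30 | 0.380 | 0.350 | -0.030 |
| 0.40 | 0.40 | 0.400 | 0.400 | 0 |
| 0.30 | 0.50 | 0.420 | 0.450 | +0.030 |

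In the third row the shift is 0.0375/0.350 = 10.7% of the PRE value. The same step in reverse occurs between FU8 and FU12.

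**Step 4: the FU12 contrast.** PRE, FU12 and FU52 all have 10 components, so change between them carries no composition artefact. Only the weighting differs from an 8-component index. If the between-arm difference is *D* on depression/worry and *E* on the other domains, then the contrast changes by (0.40*D* + 0.60*E*) - (0.25*D* + 0.75*E*) = 0.15 × (*D* - *E*). This is zero when the arms differ equally in all domains.

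**Step 5: after the fix.** With PHQ-2 and GAD-2 only, there are 8 components at all five points. Each weighs 12.5%, depression plus worry weighs 25% throughout, and no item counts twice.

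**The case against.** The best defence is that the section on symptoms opens by saying that shortened questionnaires measure symptoms. If that governs the index, only PHQ-2 and GAD-2 enter and the problem disappears. Table 2 is a schedule, not a list of index components, and it also lists WHODAS in two nested versions. The long forms carry the algorithm cut-offs (8 for PHQ-9, 9 for GAD-7) and the short forms carry none, which could mean long forms for the algorithm and short forms for follow-up.

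This reading is possible but weak. The article says that the symptom scales also feed the algorithm through the Table 2 cut-offs. For depression and generalised anxiety only the long forms have a cut-off, so the article's own use of the term includes them. A third reading, the long form where available and the short form otherwise, removes the double counting but still changes instrument between visits.

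It can also be said that scoring detail belongs in an analysis plan that is not shown. That would answer a complaint about a missing rule. Here the rule and its exceptions are stated, and the point is what they produce.

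Three objections on consequences stand:

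- The formula is the same in both arms, so the shift at FU4 and FU8 is largely common to them.
- The direction is not known.
- The aim of limiting overlap is stated only for stress and exhaustion; applying it to PHQ and GAD is an inference from the plan's reasoning.

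**Conclusion.** The point holds for the rule as worded: 10 components against 8, and 40% against 25% weight for depression plus worry, with nested items counted twice. These counts need no assumption beyond reading the rule together with Table 2. The size of the artificial shift, -0.15 × (*a* - *b*), rests on means that the documents do not give and on short and long forms scoring alike after normalisation.

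The consequence is limited to a secondary outcome. Within-arm trajectories that use FU4 or FU8 are distorted. The randomised FU12 contrast is changed only through the extra weight on depression and worry, and WHODAS-8, the primary outcome, is unaffected.

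A reader might go further in three ways that the documents do not support:

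- That the index will show a dip at FU4 and FU8 and a rebound at FU12. This needs depression/worry scores above the other domains; with equal scores there is no shift, and with the order reversed there is a rise.
- That the 12-week comparison of the arms is biased by changing composition. PRE and FU12 have the same composition.
- That the separate primary symptom measure needs a prescribed PHQ or GAD version. No error is shown there; the choice would be a preference.

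**What to change.** Replace the open wording with a closed list. The general symptom index is the mean of the same 8 normalised components at PRE, FU4, FU8, FU12 and FU52: PHQ-2, GAD-2, ISI-2, the mean of PSS-3 and KEDS-3, OCD-3, PDSS-SR-2, SHAI-3 and Mini-SPIN. Report PHQ-9 and GAD-7 separately at PRE, FU12 and FU52. PHQ-2 and GAD-2 are the only versions scheduled at all five points, so they are the ones that keep the index constant.

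The cost is one sentence, fixed before analysis, and no new data. The downside is that depression and worry enter the index through two-item scores.
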